## Abstract

**Background:**

Reducing current clinical symptoms and the risks of future exacerbations is the main goal of stable COPD management. Traditional Chinese medicine has unique advantages in chronic disease management. YuPingFeng (YPF), as a classical prescription, has been proven to reduce the risk of exacerbations, but there is a lack of high-quality evidence for the assessment of clinical symptoms and quality of life, particularly for the assessment of treatment response of microecology and immunity.

**Methods/design:**

This is a prospective, multicentre, randomized, double-blind, placebo-controlled clinical trial. A total of 316 eligible subjects with moderate to severe COPD will be randomized 1:1 to receive YPF or placebo. Participants will receive either YPF or a placebo at 5 g three times daily for 52 weeks. The primary outcome will be the change in the COPD Assessment Test (CAT) score after 52 weeks of treatment. Secondary outcomes will include changes in the St George's Respiratory Questionnaire (SGRQ) score and clinical symptom score, among others. Outcomes will be measured at each visit. The study will continue for 52 weeks and will include six visits to each subject (at day 0 and weeks 4,12,24,36 and 52). In the event of exacerbations, subjects will be required to go back to the hospital once on the first day of exacerbation or when their condition permits.

**Discussion:**

This trial will provide research methods to evaluate the clinical efficacy, safety, and the possible mechanism of YPF in the treatment of stable moderate-to-severe COPD patients. In addition, we hope to provide more possibilities for TCM to participate in the management of stable COPD.

**Trial registration:**

The trial was registered at the Chinese Clinical Trials Registry on 3 June 2022 (ChiCTR2200060476; date recorded: 3/6/2022, https://www.chictr.org.cn/).

## Background

Chronic Obstructive Pulmonary Disease (COPD) has become a major chronic disease that seriously endangers public health. The World Health Organization (WHO) predicted that the prevalence of COPD will continue to rise over the next 40 years and that by 2060 there will be more than 5.4 million deaths annually from COPD and related conditions [1, 2]. At present, the number of people with COPD has reached 99.9 million [3], making it the third leading cause of death in China and the second leading cause of disease burden in terms of disability-adjusted life years [4, 5]. Therefore, in order to reduce the incidence of acute exacerbations of COPD (AECOPD), improve the quality of life, reduce the mortality of patients, and reduce the social and economic burden, the treatment and management of stable COPD must be given attention. Currently, bronchodilators (β2 receptor agonists, anticholinergic drugs, combined bronchodilators, etc.), glucocorticoids, methylxanthine, etc. are commonly used drugs for the treatment of COPD [2]. However, while bronchodilators and glucocorticoids can relieve symptoms, they cannot effectively reduce oxidative stress or improve the downward trend in lung function [6–8]. In addition, COPD-related inflammation has a limited response to inhaled corticosteroids (ICS), and ICS alone do not prevent a sustained decline in FEV1 or mortality in COPD patients [9]. Long-term use of ICS is even associated with side effects, including osteoporosis, bleeding from peptic ulcers, hypertension, oral candidiasis, hoarseness, and pneumonia [9–12]. It can be seen that the commonly used drugs for the treatment of COPD have certain limitations and side effects, which create difficulties in the management of stable COPD. More importantly, no breakthrough new drugs have been approved for COPD, indicating that there is a huge unmet need in the pathogenesis of COPD and the development of preventive and trerapeutic drugs. In particular, safer and more effective preventive drugs need to be developed for earlier intervention, while making efficient use of scarce healthcare resources.

Traditional Chinese Medicine (TCM) is the greatest treasure trove waiting to be discovered by modern medicine. YuPingFeng (YPF), one of the classic TCM formulas with a tonic effect, is composed of Astragali Radix, Atractylodes Macrocephala Koidz, and Radix Saposhnikoviae. Recent pharmacological studies have shown that YPF can activate mucosal immunity, resists hormone-induced immunosuppression, and is recommended to be used in the treatment of stable COPD [13, 14]. A multicentre, randomized, double-blind, placebo-controlled clinical study we conducted confirmed that the combination of conventional treatment with YPF granules for 52 weeks significantly reduced the risk of acute exacerbations by 32.3% in moderate-to-severe COPD patients [15], but did not investigate the mechanism. Some small sample sizes or observational trials have shown that this drug may regulate immune function, improve lung function, and improves the quality of life [16, 17], but high-quality evidence-based evidence is still lacking. In recent years, the heterogeneity of AECOPD has been gradually recognized and preliminarily explored. The clinical phenotype differentiated by peripheral eosinophils is one of the important phenotypes of AECOPD. Eosinophils are generally considered to be a type of white blood cell associated with allergic diseases. In allergic disease, YPF has been shown to have good effects in both improving symptoms and controlling relapses [18–20]. A number of studies have also shown that YPF inhibits eosinophil activity and also inhibits eosinophil proliferation [21, 22]. We hypothesized that YPF may have a more pronounced clinical benefit on the eosinophilic phenotype of AECOPD. Therefore, we designed a prospective, multicentre, randomized, double-blind, placebo-controlled clinical trial based on eosinophil phenotypic stratification to evaluate the efficacy of YPF on clinical symptoms and quality of life, safety, and therapeutic response in microecology and immunity in stable COPD. We hoped to confirm the preventive and trerapeutic effects of YPF from different perspectives and to discover its possible mechanism.

## Method

### Study design

This is a prospective, multicentre, double-blind, randomized controlled trial to evaluate the efficacy and safety of YPF granules in improving the clinical symptoms of stable COPD and to explore the underlying mechanism. Based on the exclusion and inclusion criteria, a total of 316 eligible subjects will be enrolled and randomly assigned to the YPF treatment group or control group in a 1:1 ratio. The study flowchart is shown in Fig. 1. Following informed consent and collection of baseline information, treatment will be administered for 52 weeks according to stratified block randomization. All subjects will return to the hospital once on day 0 and at weeks 4,12,24,36, and 52 to complete the assessment of their symptoms, signs, and quality of life scores (assessed by CAT, SGRQ, laboratory indicators, etc.). If subjects have an acute exacerbation, an additional visit will be made on the first day of the exacerbation or as conditions permit. The specific assessments at each visit are detailed in Table 1.

**Fig. 1 Fig1:**
[figure not shown]
Flowchart of the trial design

**Table 1 Tab1:** Study schedule of specific assessments

	**Enrolment** **(Day -28 to 0)**		**Follow-up(± 3 days) **^**a**^					
Visit period	Screening stage ^c^	Visit 0	Visit 1	Visit 2	Visit 3	Visit 4	Visit 5	Additional visit ^**b**^
Visit time	Day -28 to 0	day 0	week 4	Week 12	Week 24	Week 36	Week 52	–
**Basic condition**								
Signing informed consent	●							
Demographic information ^**d**^	●							
General clinical information ^**e**^	●							
**Efficacy assessments**								
SGRQ scale		●	●	●	●	●	●	●
CAT scale		●	●	●	●	●	●	●
Symptom scale	●	●	●	●	●	●	●	●
Number of exacerbations and duration			●	●	●	●	●	●
Number of hospitalizations and reasons			●	●	●	●	●	●
Constitution of TCM^f^		●			●		●	
**Safety assessments**								
Vital sign	●	●	●	●	●	●	●	●
Physical examination	●		●	●	●	●	●	●
HCG	●							
Glycosylated Hemoglobin	●							
Lung function	●							
Blood routine	●				●		●	
NGHX	●				●		●	
Serum biochemicals	●				●		●	
Adverse events recorded		●	●	●	●	●	●	●
**Exploratory assessments **^**g**^								
Microecology of the respiratory tract		●	●	●	●	●	●	●
Herpesvirus infection		●	●	●	●	●	●	●
Classification and counting of lymphocytes		●	●	●	●	●	●	●
Inflammatory cytokines		●	●	●	●	●	●	●
Immunoglobulin		●	●	●	●	●	●	●
**Others**								
Starting time of treatment		●						
Combination therapy		●	●	●	●	●	●	●
Issue medications and diary cards		●	●	●	●	●		
Recycle medications and diary cards			●	●	●	●	●	
eCRF	●	●	●	●	●	●	●	●

*SGRQ* The St George's Respiratory Questionnaire, *CAT* COPD assessment test, *HCG* Human chorionic gonadotropin, *NGHX* Urine dry chemical analysis, *eCRF* Electronic case report form

^a^The time window of follow-up is ± 3 days, while the additional visit is ± 1 day;

^b^For additional visits, if subjects have an acute exacerbation, an additional visit will be taken on the first day of the exacerbation;

^c^The time window of screening is -28 ~ 0 days, and Day 0 is the day on which medication is started. During the screening period, the results of HCG, GHb, NGHX, lung function, blood routine, and serum biochemicals can be accepted within 7 days;

^d^Demographics, including age, gender, height, weight, marital status, ethnic origin, etc.;

^e^General clinical information, including medical history, course of the disease, number of exacerbations within the past year, etc.,

^f^Constitution of TCM [23]: based on the Classification and Determination of Constitution in TCM(ZYYXH/T157-2009) released by the China Association of Chinese Medicine;

^g^For the exploratory assessments, the chief unit is required to conduct tests every visit, while others are required on Day 0, Week 24, Week 52, and additional visits. Sputum, throat swabs, and blood samples are detected and analyzed by the central laboratory and the results are uniformly recorded, but not included in the CRF

### Sample size

According to the results of the previous study [15], the mean difference in CAT scores between the YPF group and the control group was 2.2, and the combined standard deviation was 6.2184. The sample size was calculated accordingly, with an α risk of 0.05 and a β risk of 0.2 in a two-sided contrast. This study required a minimum of 252 subjects. Allowing for 20% attrition, a total sample size of 316 subjects was required, 158 in the treatment group and 158 in the control group.

### Study sites and participant recruitment

Subjects will be recruited consecutively from eight university hospitals or hospitals with adequate experience of RCTs. These hospitals are located across China in the provinces of Guangdong, Yunnan, Shanghai, Guizhou, Shanxi, Hunan, and Xinjiang. The total recruitment period is planned to be 28 months, from 23/5/2022 to 24/9/2024. In order to screen suitable patients as quickly as possible, the eight participating hospitals will post recruitment advertisements on their websites and bulletin boards. The advertisements will include a brief description of the required subjects, study drugs, medical examinations, and how to participate in the trial. The First Affiliated Hospital of Guangzhou Medical University, as the lead institution, will recruit subjects first. Patients who meet the inclusion criteria but do not meet the exclusion criteria will be eventually be enrolled, and then treated and followed up according to the study protocol.

### Inclusion criteria

Aged 40 to 80 years, male or female;Patients meet the diagnostic criteria for COPD (Guidelines for the diagnosis and management of chronic obstructive pulmonary disease (revised 2021 version) [24].)Patients clinically diagnosed with moderate to severe COPD (based on the 2021 GOLD guidelines), with airflow limitation including the following: a postbronchodilator fixed ratio FEV1/FVC ≤ 70%, 30% ≤ FEV1 < 80% predicted;The single score of expectoration ≥ 1 point;Patients with a history of exacerbations in the past year: ≥ 2 moderate acute exacerbations or ≥ 1 severe acute exacerbation;Patients were in stable condition in the past 4 weeks, without respiratory tract infection and AECOPD;Volunteered to participate in the trial, and signed the written informed consent.

### Exclusion criteria

The interval between clinical diagnosis of COPD and enrolment in the trial is ≤ 12 months;Patients needed long-term regular oxygen therapy, and oxygen inhalation for more than 15 h daily;Patients have not previously received live attenuated vaccines, but plan to receive live attenuated vaccines during the trial;Patients with lung transplantation or pneumonectomy, patients scheduled for lung transplantation or pneumonectomy, or patients enrolled in a pulmonary rehabilitation programmePatients diagnosed with or with a history of asthma (according to the 2018 GINA guidelines or other recognized guidelines);Patients with other significant lung diseases (such as pulmonary interstitial fibrosis, active tuberculosis, lung tumors, etc.);Patients with severe heart diseases, liver, or kidney disease;Patients with poorly controlled insulin-dependent diabetes mellitus (HBA1c ≥ 8.0%);Immunocompromised patients;Patients who have participated in clinical trials of other drugs within 3 months prior to enrolment or who are regularly taking proprietary Chinese patent medicine with the same efficacy as YPF.Patients who are allergic to any components of the study drug;Patients with serious neurological, hematological, gastrointestinal, cerebrovascular diseases, malignant tumors, and other current or previous serious diseases that could interfere with the study or require treatment that could interfere with the study;Pregnant or breastfeeding women, and male patients planning to become fertile;Patients considered by the investigator to be unsuitable for participation.

### Withdrawal and discontinuation criteria

All eligible patients have the right to withdraw from the trial at any time. During the trial, the following situations should be treated as withdrawals:Serious complications, significant physiological changes, serious adverse events, and other serious events that occur during the trial.Poor subject compliance of subjects (such as taking drugs in violation of the prescribed dose)Subjects are unwilling to continue the trial and ask to withdraw from the trialRefusal to accept medication or examination and lose of visitors.Subjects become unblinded halfway through the trial.

The reasons for subjects’ withdrawal or discontinuation from the trial should be documented in detail. For those who withdrawn from the trial because of adverse events, the investigators should take appropriate treatment measures according to the subject’s actual situation, and try to complete the last test for subsequent statistical analysis.

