### Outcome measurements

#### Efficacy indicators

The primary outcome is the changes in the COPD assessment test (CAT) score after 52-week of treatment. Specifically, the differences between the total CAT score at week 52 and baseline will be calculated respectively for the experimental and the control groups, respectively, and the difference between the two groups will be compared. The secondary outcomes include the following eleven indicators:Annualized rates of moderate or severe COPD exacerbations. The measure is the number of acute exacerbations of moderate or severe COPD during 52-week treatment/total participants in the group. The definition of an acute exacerbation of COPD (AECOPD): is an acute change in a patient’s baseline dyspnea, cough, and/or sputum beyond day-to-day variability sufficient to warrant a change in therapy. The severity of AECOPD is graded as follows: (1) Mild: requires only increased treatment with short-acting bronchodilators, such as short-acting β-receptor agonists (SABA); (2) Moderate: requires increased antibiotics and/or oral glucocorticoid hormone; (3) Severe: requires hospitalization or emergency treatment, may be complicated by acute respiratory failure.All-cause admission rate and admission rate due to acute exacerbation. All-cause admission rate = (total number of admission during 52-week treatment)/ (total number of participants in the group) and the admission rate due to acute exacerbation = (number of admission due to acute exacerbation during 52-week treatment)/ (total number of participants in the group).The changes in the St George's Respiratory Questionnaire (SGRQ) score.The proportion of patients with an SGRQ response (defined as an improvement of ≥ 4 units from baseline).The changes in the CAT score.The median time to the first exacerbation of COPD and the median time to the first exacerbation of moderate or severe COPD during treatment.Duration and time interval of acute exacerbations compared with the control group.Annualized rates of acute exacerbations of COPD of different severity.The changes in clinical symptom score (Table 2) compared with the control group.The changes in the individual clinical symptom score compared with the control group.Frequency of first-aid drug use.The changes in TCM constitution from the baseline to week 24 and week 52.

**Table 2 Tab2:** The clinical symptom assessment scale

Item	Symptoms Assessment rating scale			
	0 (none)	1 (mild)	2 (moderate)	3 (severe)

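### The withdrawal rule does not separate stopping medication from ending follow-up, so it can cut off patients after a severe exacerbation and may use up the 20% attrition allowance

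*Protocol article*

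**What the plan says.** All of this is in the protocol article.

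- **Withdrawal and discontinuation criteria.** The situations counted as withdrawal include "Serious complications, significant physiological changes, serious adverse events, and other serious events that occur during the trial", "Poor subject compliance of subjects (such as taking drugs in violation of the prescribed dose", a subject's own wish to leave, refusal or loss to follow-up, and unblinding during the trial. For those who leave because of an adverse event, investigators should "try to complete the last test for subsequent statistical analysis". No timing is attached to that test, and no similar request is made for the other reasons.
- **Efficacy indicators.** The primary outcome is the change in CAT from baseline to week 52. Secondary outcomes include exacerbations by severity, all-cause admissions, admissions for exacerbation, and the duration of and interval between exacerbations. The top severity grade is "Severe: requires hospitalization or emergency treatment, may be complicated by acute respiratory failure". The exacerbation and admission rates are events over 52 weeks divided by all participants in the group.
- **Study design and Table 1.** An additional visit takes place at an acute exacerbation, and exacerbations and hospitalizations are recorded at every visit after baseline.
- **Randomization, blinding and unblinding.** Emergency unblinding is tolerated up to a rate of 20%.
- **Sample size.** "This study required a minimum of 252 subjects" and "Allowing for 20% attrition, a total sample size of 316 subjects was required".

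**The concern.** The rule acts on what happens after randomisation, and it does not distinguish stopping study medication from leaving the trial. A hospitalized exacerbation is naturally read as a serious event. A site that follows the text as written could therefore end follow-up at the event that the secondary outcomes are meant to count, possibly repeatedly.

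Three things are at stake:

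- **Event outcomes.** The rates divide by all participants, not by time observed. A subject who leaves early still counts in full in the denominator while later events are lost.
- **Primary outcome.** The week-52 CAT would be missing in sicker subjects because they were sicker. The Background reports a 32.3% lower exacerbation risk with YPF in the preceding trial. If that recurs, more placebo subjects leave, the remaining placebo group looks healthier, and the comparison is biased against YPF.
- **Power.** One 20% allowance has to cover every reason for loss, including those the rule itself creates.

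This cannot be left to a later analysis plan, because visits that were never made cannot be recovered.

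**Working it through.** **1. Reproduce the plan's sample size.** Inputs from Sample size: "the mean difference in CAT scores between the YPF group and the control group was 2.2, and the combined standard deviation was 6.2184", "with an α risk of 0.05 and a β risk of 0.2 in a two-sided contrast". Allocation is 1:1.

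- n per arm = 2 × (1.96 + 0.8416)² × 6.2184² / 2.2² = 125.4, rounded up to 126, so 252 in total.
- 126 / (1 − 0.20) = 157.5, rounded up to 158 per arm, so 316 in total.

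Both stated figures reproduce, so the sample-size arithmetic is correct. The allowance is 316 − 252 = 64 subjects (20.3%) for all causes together.

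**2. Set the withdrawal rule beside the unblinding tolerance.** This step needs no assumed event rate, only that the 20% is taken over all 316 subjects.

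- 316 × 0.20 = 63.2, about 63 subjects.
- 316 − 63 = 253 remain, one more than the required 252.

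At the ceiling the protocol tolerates, nothing is left for adverse events, poor compliance, refusal or loss to follow-up.

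**3. Withdrawals through severe exacerbation (assumed rates).** The documents give no rate. Assume a negative binomial count with mean μ per patient-year and dispersion 1, with μ from 0.15 to 0.40 in the whole trial. The share with at least one event is 1 − 1/(1 + μ).

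Power is Φ(δ/σ × √(m/2) − 1.96), with m per arm and δ/σ = 2.2/6.2184 = 0.3538.

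| Scenario | Lost | Remaining | Power |
|---|---|---|---|
| μ = 0.15: share 13.0% | 41 | 275 | about 83% |
| Full allowance used | 64 | 252 | about 80% |
| μ = 0.40: share 28.6% | 90 | 226 | about 76% |
| 30% total loss, all causes | 95 | 221 | about 75% |

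The μ rows count this cause alone and treat every such subject as lost to the week-52 comparison.

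**4. Adding other losses (also assumed, causes independent).**

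- 10% serious events and 10% other: 1 − 0.90 × 0.90 = 19.0% lost, 256 remain, power 80.8%. The allowance holds.
- 20% and 10%: 1 − 0.80 × 0.90 = 28.0% lost, 228 remain, power 76.1%. It does not.

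**5. Direction of the bias (illustration).** Assume 0.40 severe events per year on placebo, and apply the 32.3% reduction to severe events: 0.40 × 0.677 = 0.271 on YPF.

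- Share withdrawn: 0.40/1.40 = 28.6% on placebo and 0.271/1.271 = 21.3% on YPF, about 45 against 34 of 158.
- If each subject can contribute at most one severe event, the apparent reduction is 1 − 21.3/28.6 = 25% instead of 32%.

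Under these assumptions the rule shrinks the observed benefit.

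**The case against.** The strongest reply is that the article never says an exacerbation is a reason for withdrawal. The additional visit, the recording of hospitalizations at each visit and the interval between exacerbations all presume that such patients stay in. Adverse events are defined there as unexpected findings, so an exacerbation captured as an efficacy endpoint is not clearly a serious adverse event. This stands in part: ending follow-up at the first severe exacerbation is the natural literal reading but is not written. It does not remove the problem, because the category of other serious events is broad and carries no exception, and two sections then instruct sites differently.

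A reader might also infer three stronger points that the documents do not support:

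- **That the attrition allowance is certainly exhausted.** No event rates are given. The assumed range of 41 to 90 withdrawals straddles 64, and some plausible combinations of losses fit within the allowance.
- **That patients are removed for having the primary outcome.** The events concerned are secondary outcomes. The primary outcome is affected through missing data.
- **That withdrawn subjects, including non-compliers, are excluded from analysis.** A full analysis set is named alongside the per-protocol set, and its definition may sit in a document not shown. A last test is sought after adverse-event withdrawal. Silence about the other reasons is weaker evidence than a stated refusal to collect.

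What remains is that a full analysis set cannot supply a week-52 CAT or later admissions that were never collected, and that a last test at no fixed time need not be a week-52 value.

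**Conclusion.** The point holds as a conflict within the protocol article with consequences for the data. The withdrawal criteria, taken literally, can end outcome collection after a secondary-outcome event. They clash with the exacerbation visits, with the 52-week counts and with the tolerated unblinding rate. The expected effects are truncated exacerbation and admission counts and an informatively missing week-52 CAT, with the likely bias against YPF if it reduces exacerbations.

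The allowance may be exceeded, but this is not shown as fact. The firmest figure is that unblinding at the tolerated ceiling would by itself take about 63 of the 64 available losses. The power figures of about 83% to 76% rest on the assumed severe-exacerbation rates and dispersion, count that cause alone, and assume that no usable week-52 CAT is obtained. The stated 252 and 316 are correct for their inputs.

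**What to change.** Amend Withdrawal and discontinuation criteria, and reconcile it with Study design, Table 1, Efficacy indicators and Randomization, blinding and unblinding. State that:

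- meeting one of the listed criteria does not end outcome collection;
- such subjects attend all scheduled visits to week 52, with CAT, SGRQ, exacerbations and admissions recorded, unless they withdraw consent or are lost to contact;
- they are analysed in the group to which they were randomised.

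The 20% allowance should also be justified against the losses expected once the rule is clear. Whether study medication stops after any of these events is a clinical decision and is not addressed here.

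The cost is a protocol amendment and a memo to sites. Staff must keep bringing off-treatment subjects to visits that are already scheduled, and some off-treatment data will enter the full analysis set.
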